### Sample size considerations

The study is powered to demonstrate differences in primary outcome between individual study subjects; the calculated sample size will be adequate to detect a clinically important effect of vitamin D on PWV (reduction of 1m/sec). The mean difference of 1m/s is clinically meaningful in that it has been demonstrated to confer a 34% increased risk of CV mortality in a cohort of CKD stage 5 patients on dialysis [33, 34]. A sample size of 105 (35 placebo arm and 70 treatment arm) without attrition will provide 85% power to demonstrate the mean PWV difference of 1m/s between arms, with 0.05 target alpha for a two sided test. Thus, recruitment and enrolment of 128 subjects will allow for ~15% attrition.

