### Statistical analysis

The primary analysis will compare vitamin D (25 vitamin and 1,25 vitamin D) therapies versus placebo for the primary outcome defined as the change of PWV from baseline to 6 months by covariance analysis (ANCOVA); where the 6 month measurement of PWV will be the dependent variable, allocated treatment the independent variable, and baseline PWV the baseline covariate [29, 36, 37]. Analyses will be considered statistically significant if the p-value is <0.05 for allocated treatment. In case of violation of ANCOVA assumptions we will use a mixed model approach.

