We expect to find vitamin D to have an impact on vascular stiffness and BP irrespective of serum vitamin D levels. The impact will be greatest on those with highest PWV. The data generated herein will permit the development of a set of phenotypes using clinical and biomarker data. Such that characterization of patients according to PWV, BP, FGF-23 and vitamin D levels will be possible, and results of treatment strategies will be examined within the phenotype category. This information will be significant for future enrolment in clinical trials. The biomarker analyses will aid in explaining any dissociation found between BP and vascular stiffness.

Before large randomized trials can be developed, these unanswered questions regarding the mechanism of disease require resolution to ensure pertinent study design. This is an ‘intermediate’ study which fully examines the physiological consequences of different vitamin D therapies in CKD populations. The findings will be used to understand physiological mechanisms, generate further hypotheses for testing, and ultimately contribute to evidence base studies which will inform clinical practice.

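### The primary ANCOVA gives way to an unspecified mixed model if its assumptions fail; that switch depends on outcome data and, in the usual forms, does not cure the failure and can cost power

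*Protocol article*

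**What the plan says.** The Statistical analysis section of the protocol article defines the primary model as an ANCOVA "where the 6 month measurement of PWV will be the dependent variable, allocated treatment the independent variable, and baseline PWV the baseline covariate". It contains no treatment-by-baseline term, and success is a p-value below 0.05 for allocated treatment. The section closes with the fallback: "In case of violation of ANCOVA assumptions we will use a mixed model approach". It names one remedy for every kind of violation, and says neither how a violation is judged nor which mixed model is meant.

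Three other places bear on this:

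- The Discussion predicts: "The impact will be greatest on those with highest PWV".
- Variables measured gives three PWV time points (pre-washout, baseline, post treatment), with triplicate readings. Only one is after treatment.
- Sample size considerations states: "A sample size of 105 (35 placebo arm and 70 treatment arm) without attrition will provide 85% power" for a 1 m/s difference. The primary comparison is therefore unbalanced, 1 to 2.

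**The concern.** The fallback sits inside the definition of the primary analysis. If diagnostics on the trial's own outcome data look poor, the planned estimator is replaced, so which p-value is primary depends on the data.

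The replacement is also poorly matched to the problem. ANCOVA as written assumes a linear relation with baseline, one slope for both groups, equal residual variance, normal residuals and independent observations. A standard Gaussian mixed model on one baseline and one follow-up value keeps linearity, normality and a covariance common to the arms.

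The Discussion's prediction is a treatment-by-baseline interaction, that is, unequal slopes. The investigators' own expectation can therefore set off the switch. At stake are the power claimed for the primary test and, if the arms differ in variance, its type I error.

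**Working it through.** **Inputs.** From the article: 35 v 70 evaluable patients, a 1 m/s difference, two-sided alpha 0.05, 85% power. The article gives no SD or slope, so these are assumptions. For power: baseline SD 3 m/s, residual SD 1.6 m/s, placebo slope 0.8. For unequal variances: residual SDs between 1.2 and 2.0 m/s. Interactions are in m/s of effect per m/s of baseline PWV.

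**1. The plan's own figure.** The SD implied by 105 patients is 1 / [(1.960 + 1.036) × √(1/35 + 1/70)] = 1 / (2.996 × 0.2070) = 1.61 m/s (1.60 with the t distribution). The assumed residual SD of 1.6 thus matches the plan's power.

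**2. What the usual mixed models reduce to (complete data).**
- Common baseline mean and a common unstructured covariance: the likelihood splits into f(baseline) × f(month 6 | baseline, treatment), so the treatment estimate is the ANCOVA estimate.
- Free baseline means with a random intercept: the estimate is the difference in mean change. In one simulated dataset the mixed model and the change-score difference both gave -1.184; ANCOVA gave -1.258.

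**3. What the prediction means.** With an average effect of -1 and an interaction of -0.2, the effect is -1 + 0.2 × 3 = -0.4 m/s at one SD below mean baseline and -1 - 0.2 × 3 = -1.6 m/s at one SD above. At -0.3 it is -0.1 and -1.9.

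**4. Power of the random-intercept form, by formula, at interaction -0.3.** The treated slope is 0.8 - 0.3 = 0.5.
- Variance of change, placebo: (0.8 - 1)² × 9 + 2.56 = 2.92.
- Variance of change, treated: (0.5 - 1)² × 9 + 2.56 = 4.81.
- Pooled: (34 × 2.92 + 69 × 4.81)/103 = 4.19, so the model SE is √(4.19 × 3/70) = 0.424.
- True SE: √(2.92/35 + 4.81/70) = 0.390.
- Power: Φ[(1 - 1.983 × 0.424)/0.390] = Φ(0.41) = 66%.

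The same steps at -0.2 (treated variance 4.00) give 72%.

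**5. Power by simulation, 35 v 70, true average effect -1 m/s.** The switch is modelled as a 5% test of equal slopes followed, if significant, by the random-intercept model.

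| | Interaction -0.2 | Interaction -0.3 |
|---|---|---|
| ANCOVA throughout | 84% | 81% |
| ANCOVA, HC3 | 82% | 79-80% |
| Random-intercept model throughout | 72% | 65-68% |
| ANCOVA with switch | 79% | 69% |
| Slope test significant | about 42% | about 75% |

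Loss from the switch: 84 - 79 = 5 points and 81 - 69 = 12 points. With an average effect of zero and interactions of -0.1 to -0.3, ANCOVA was unbiased and rejected 4.5-5.1% of the time.

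**6. Unequal residual variances, equal slopes, no effect.** By formula for ANCOVA with placebo SD 1.8 and treated SD 1.2: pooled variance (34 × 3.24 + 69 × 1.44)/103 = 2.034; model SE √(2.034 × 3/70) = 0.295; true SE √(3.24/35 + 1.44/70) = 0.336. Type I error is 2 × [1 - Φ(1.983 × 0.295/0.336)] = 2 × [1 - Φ(1.74)] = 8.2%. Simulation, over repeated runs:

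| Residual SD, placebo v treated | ANCOVA | Random-intercept | ANCOVA, HC3 |
|---|---|---|---|
| 1.8 to 2.0 v 1.2 | 8.0-9.8% | 7.6-9.0% | 4.8-5.2% |
| 1.2 v 1.8 | 2.5-2.7% | – | – |

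A model with arm-specific slopes and variances, run with the placebo SD at twice and at half the treated SD of 1.6, gave 5.5% and 5.0%. ANCOVA gave 11.4% and 1.8%, and the random-intercept model about 11% and 2.2-2.5%.

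**The case against.** **The form of the mixed model may be in an analysis plan that is not shown.** That is fair, and leaving out the covariance structure is not the criticism. What the article does fix is that the primary estimator changes when assumptions fail, with one remedy for every failure.

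**A mixed model is not useless.** This stands. A reader might infer that no mixed model could repair a violated assumption. That is wrong: a form with arm-specific covariance handles both unequal slopes and unequal variances, and a mixed model can deal with non-independence such as the triplicate readings. With the attrition of about 15% that the article allows for, a likelihood model can also use patients without a month-6 value.

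**The Discussion's prediction does not invalidate ANCOVA.** This also stands. Under randomisation, moderate slope differences left the average effect unbiased and the test near 5%. Even slopes of 0.9 v 0.4, with baseline SD 2.5 and residual SD 1.2, gave only 6.0-6.8%. That gap means the effect changes by 0.5 × 2.5 = 1.25 m/s per baseline SD, more than the whole target effect. It is a reason not to leave ANCOVA on account of unequal slopes.

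**The switch need not fire when the trial's hypothesis is true.** Correct. The primary question concerns the average effect, which can exist with equal slopes, and a slope test would often miss the interactions considered here.

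**The type I error figures rest on assumed SDs.** Correct. Nothing in the article suggests that the placebo arm is the more variable one, and if the treated arm is, the test becomes conservative.

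**Conclusion.** The concern holds in a limited form. The switch makes the primary estimator depend on the outcome data, and the usual mixed models for one follow-up visit do not cure unequal variances. The random-intercept form also loses power when slopes differ. Under the assumptions above, the loss is about 5 to 12 points at interactions of -0.2 to -0.3. This further assumes that a 5% slope test triggers the switch, which the article does not say.

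Under unequal residual variances, type I error for ANCOVA could be about 8-10% or about 2.7%, depending on which arm is more variable; HC3 holds about 5% where it was examined. A reader might infer that this trial's type I error is inflated, or that the treatment p-value would refer to an effect at a PWV of zero. The documents support neither: they give no SDs by arm, and the stated model has no interaction term.

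The change is worth making because a single pre-specified ANCOVA with robust standard errors is better and cheap.

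**What to change.** - Delete the sentence that switches models.
- Keep ANCOVA of month-6 PWV on the pooled treatment contrast and baseline PWV as the only primary model, whatever the diagnostics show, with HC3 heteroscedasticity-robust standard errors.
- Test the Discussion's prediction as a secondary treatment-by-baseline interaction, with baseline PWV centred at the trial mean so that the treatment term remains the average effect.
- Use any mixed model, rank-based ANCOVA or permutation test only as a sensitivity analysis, with its form and covariance stated in advance.

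This takes a few sentences and no extra patients. When all ANCOVA assumptions hold, HC3 raises the standard error by about 2% (0.253 v 0.249 in simulation with residual SD 1.2), or about 1-2 points of power.

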### Strengths and weaknesses

It is conceivable that the therapies as administered may not have an impact on our chosen outcomes of interest: vascular stiffness, BP or proteinuria (primary or secondary). The 6 month time period may not be sufficient exposure to demonstrate the effect of the vitamin D treatment, or the expected difference in PWV changes/reductions between the groups is different and thus the study may be underpowered. However, given that this study uniquely examines non dialysis advance stage CKD patients, using fixed dose drug administration schedules, physiological measurements and biochemical measurements serially over time, the study will add to the growing body of literature regarding the use of vitamin D supplementation in CKD population. If positive, it will inform future larger studies looking at additional measures such as LV mass, or function over time in relation to PWV, and will add to our understanding of the physiology of vascular changes in CKD. Given the current state of knowledge, and the plethora of studies, reviews, and meta-analysis that fail to consistently demonstrate a benefit to Vitamin D supplementation, there are no ethical issues conducting a placebo-controlled trial.

## Discussion

There is an accumulating body of evidence that vitamin D acting on multiple aspects of physiological processes involved in the pathogenesis of CVD and thus may be an important therapeutic strategy in CKD. Studies conducted to date have failed to demonstrate significant impact of hormone supplementation on outcomes. Cholecalciferol has been studied in 60 patients on hemodialysis, who were known to be 25 OHD_3_ deficient and did not show any change in PWV [38]. Other studies conducted in both dialysis and non dialysis CKD patients, also included were those with demonstrable deficiencies for limited time periods (8 weeks) showed changes in serum levels of 25 and 1, 25 Vitamin D levels [39–42]. Although more pronounced in non dialysis patients, other outcomes were not measured. Another study demonstrated that 25 OHD_3_ supplementation in post menopausal women did not reduce CV risk, when studied in a randomized control trial [43]. These studies were all relatively short term and focused on different questions than the ones we are attempting to answer in this study. We believe that attempting to establish a biological mechanistic effect of vitamin D supplementation on vascular function is necessary before further larger randomized controlled trials are undertaken. Given the purported differential ability of CKD patients to achieve appropriate concentrations of the active compound, the question of which supplementation is more appropriate, 25 vitamin D or 1,25 vitamin D in CKD remains controversial. The relationship of serum levels to disease, type of therapeutic supplementation (fixed dose or based on targeting serum levels) is unknown in CKD populations. Moreover, in various nephrology studies, attempts at targeting deficiencies or excesses of measured serum values in CKD patients in large randomized control trials has not met with success [44–47]. Thus, we have developed and designed a robust randomized control trial to attempt to address deficiencies in the literature, and to better understand mechanisms and complex biological interactions in this patient group.

We expect to find vitamin D to have an impact on vascular stiffness and BP irrespective of serum vitamin D levels. The impact will be greatest on those with highest PWV. The data generated herein will permit the development of a set of phenotypes using clinical and biomarker data. Such that characterization of patients according to PWV, BP, FGF-23 and vitamin D levels will be possible, and results of treatment strategies will be examined within the phenotype category. This information will be significant for future enrolment in clinical trials. The biomarker analyses will aid in explaining any dissociation found between BP and vascular stiffness.

Before large randomized trials can be developed, these unanswered questions regarding the mechanism of disease require resolution to ensure pertinent study design. This is an ‘intermediate’ study which fully examines the physiological consequences of different vitamin D therapies in CKD populations. The findings will be used to understand physiological mechanisms, generate further hypotheses for testing, and ultimately contribute to evidence base studies which will inform clinical practice.

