### Study cohort

Subjects will be drawn from a cohort of CKD patients treated according to best practices at university based tertiary care centers in Vancouver. Following written informed consent, subjects who fulfill eligibility criteria at screening (Table 1) will be randomized (1:1:1) to receive treatment of 25 vitamin D3 at 5000IU three times a week, 1,25 vitamin D (calcitriol) at 0.5ug three times a week, or placebo.

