### Statement of purpose

This physiological study will describe the impact of vitamin D therapies on a physiological measure related to CVD in CKD: vascular stiffness. Describing this mechanism would enhance the viability of testing longer term outcomes using these interventions.

*Primary questions:*Does treatment with vitamin D analogues for a period of 6 months reduce PWV in CKD patients as compared to placebo?

*Secondary questions:*Is there a difference between 1,25 vitamin D and 25 vitamin D formulations in the magnitude of reduction in PWV?Does 6 month provision of 1,25 or 25 vitamin D lead to demonstrable reductions in BP (without changes in antihypertensive medication), or proteinuria (without change in ACEi/ARB therapy) relative to placebo?What is the impact of 1,25 vitamin D and 25 vitamin D on blood levels of FGF-23, serum PTH, PO_4_ Ca, and CRP in this population? Is there a relationship between changes in vascular stiffness and changes in these biochemical/hormonal parameters?

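### Treatment results within phenotype categories would be imprecise and would not estimate effect modification; a few month-0 marker interactions in the planned ANCOVA would serve better, with a softer enrolment claim

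*Protocol article*

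**What the plan says.** The second-last paragraph of the Discussion expects vitamin D to act whatever the serum level, and to act most in patients with the highest PWV. It then says that the trial data will yield a set of phenotypes: "characterization of patients according to PWV, BP, FGF-23 and vitamin D levels will be possible, and results of treatment strategies will be examined within the" resulting phenotype category. The stated use follows: "This information will be significant for future enrolment in clinical trials".

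The article does not say how many phenotypes there will be, how they are formed, or which visit supplies the markers. Under Variables measured, PWV and the samples are taken before washout, at baseline and after treatment.

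The markers also serve as outcomes. PWV change is the primary outcome (Statistical analysis). BP is in the secondary questions, and so is FGF-23: "What is the impact of 1,25 vitamin D and 25 vitamin D on blood levels of FGF-23, serum PTH, PO_4_ Ca, and CRP in this" patient group. Under Interventions, blood levels are expected to move with treatment.

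The only sizing is for the pooled comparison: "A sample size of 105 (35 placebo arm and 70 treatment arm) without attrition will provide 85% power", for a "mean PWV difference of 1m/s between arms, with 0.05 target alpha for a two sided test".

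The Discussion also frames the study modestly: "The findings will be used to understand physiological mechanisms, generate further hypotheses for testing".

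**The concern.** The Discussion states both a method (look at treatment results inside each category) and a use (inform who is enrolled in later trials). Two things weaken the link between them.

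- **Precision.** A trial sized for one pooled contrast loses power quickly once it is divided, even into two groups.
- **Target.** The two predictions, an effect at every vitamin D level and a larger effect at high PWV, are about effect modification. A result that is significant in one category and not in another does not show that the effects differ. That needs an estimate of the difference between them, with its interval.

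At stake is the quality of any enrolment criterion carried into the larger trials that this study is meant to inform. The primary and secondary analyses are not affected.

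**Working it through.** **Inputs.** From Sample size considerations: 35 placebo and 70 vitamin D completers, difference 1 m/s, two-sided alpha 0.05, power 85%. From the Discussion: four markers, number of phenotypes *k* not given. Assumptions made here: equal-sized phenotypes, the 1:2 placebo-to-active split kept in each, normal approximation.

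**Step 1: the plan's own figure.** No SD is given, so 85% cannot be reproduced independently. It can only be solved for the SD:

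- SE needed = 1 / (1.960 + 1.036) = 0.334 m/s
- SD = 0.334 / √(1/35 + 1/70) = 0.334 / 0.207 = 1.61 m/s

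A noncentral-t calculation gives 1.60. Putting 1.61 back returns 85%, by construction.

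**Step 2: one phenotype out of *k*.** Each holds 35/*k* placebo and 70/*k* vitamin D patients.

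- SE = 1.61 × √(*k*/35 + *k*/70)
- Power for 1 m/s = Φ(1/SE − 1.960)
- 95% half-width = 1.96 × SE

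| *k* | Placebo / vitamin D | SE (m/s) | 95% half-width (m/s) | Power for 1 m/s |
|---|---|---|---|---|
| 1 (whole trial) | 35 / 70 | 0.33 | 0.65 | 85% |
| 2 | 17.5 / 35 | 0.47 | 0.93 | 56% |
| 4 | 8.75 / 17.5 | 0.67 | 1.31 | 32% |
| 8 | 4.4 / 8.75 | 0.94 | 1.85 | 18% |

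With the noncentral t, the last three powers are about 55%, 31% and 16%.

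**Step 3: sensitivity to the SD.** The same formulas with other SDs:

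| SD (m/s) | Whole trial | *k* = 2 | *k* = 4 | *k* = 8 |
|---|---|---|---|---|
| 1.4 | 93% | 68% | 41% | 23% |
| 1.61 | 85% | 56% | 32% | 18% |
| 2.0 | 68% | 40% | 23% | 13% |

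In every row, two phenotypes already fall well below the whole-trial figure.

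**Step 4: single formulations.** If treatment strategies means each formulation against placebo, the groups are 35 and 35 before division. At SD 1.61, power for 1 m/s is about 45% with two phenotypes (17.5 per arm) and 25% with four (8.75 per arm).

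**Step 5: what the predictions require.** For two equal phenotypes, the difference between their treatment effects has SE = √2 × 0.472 = 0.668 m/s. Power for a 1 m/s difference in effect = Φ(1/0.668 − 1.960) = Φ(−0.46), about 32%. So the right estimand is also hard to pin down at this size, and the remedy should not be presented as a cure for low power.

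**The case against.** The strongest reply is that this is one forward-looking paragraph in a Discussion. No phenotype question is listed in the Statement of purpose, and no phenotype analysis under Statistical analysis. The study calls itself intermediate and its findings a source of hypotheses, and Strengths and weaknesses concedes that it may be underpowered. How phenotypes are built, and at which visit, is detail that an article may leave to a fuller document. All of this stands. It makes the point a modest one, and the missing number of phenotypes and missing time point are not faults in themselves.

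Three stronger readings are tempting, and the article does not support them.

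- **Near-empty cells.** A reader might split each of the four markers in two, cross them fully, and get 105/16 = 6.6 patients per cell. The article describes no such split; the set could be two to four groups, of about 52 to 26 patients.
- **Treatment creates the groups.** A reader might infer this because the markers are also outcomes. It would be so only if post-treatment values defined the categories. Pre-randomization values are collected, and the enrolment purpose points to them, since patients can be enrolled only on what is known before treatment.
- **High risk of false responder groups.** A reader might compute 1 − 0.95⁸ = 34% or 1 − 0.95¹⁶ = 56%. Those figures count harmful-direction results as responders; for the favourable direction they are 1 − 0.975⁸ = 18% and 1 − 0.975¹⁶ = 33%. Both also presume an uncorrected test in each category, which the article does not specify.

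What the reply does not remove is the pair of affirmative statements: results examined within categories, and significance for future enrolment. The general hypothesis-generating language sits beside the enrolment claim without qualifying it.

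**Conclusion.** The point holds as a low-cost improvement. The within-category approach gives about 56%, 32% and 18% power for 1 m/s with two, four and eight equal phenotypes, against 85% for the pooled comparison, and it does not estimate the effect modification that the Discussion predicts. The figures rest on an SD of about 1.61 m/s solved from the article's own power statement, on equal-sized phenotypes and on the 1:2 split. Across SDs from 1.4 to 2.0, power with two phenotypes runs from 68% to 40%.

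It would go too far to conclude that the phenotype results cannot guide later enrolment. Imprecise findings can still suggest hypotheses, and the article says that this is their role. The supportable statement is that they cannot do so reliably, so the enrolment sentence promises more than the sample size supports.

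**What to change.** - Examine effect modification by a short prespecified set of treatment-by-marker interactions added to the planned ANCOVA: PWV, systolic BP, FGF-23 and 25 vitamin D, one at a time, each continuous. This uses all completers and addresses both predictions directly.
- Take every marker at month 0, and say so by that name. The Figure 1 caption calls the −3 month visit baseline, whereas Variables measured lists pre-washout and baseline separately, so the word baseline alone would be ambiguous.
- State that no post-randomization value defines a group.
- Report each interaction with its 95% interval and label the set exploratory.
- Reword the enrolment sentence so that the results generate hypotheses about whom to enrol.

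**Cost.** A text change and four additional models on data already collected. The downsides are a more modest promise and interaction estimates that remain imprecise, with about 32% power for a 1 m/s difference in effect between two equal groups. The gain is the right estimand and an honest interval; adequate power for subgroup claims would need a larger trial.
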